## Abstract

**Background:**

Fibromyalgia is a prevalent and disabling disorder characterized by widespread pain and other symptoms such as insomnia, fatigue or depression. Catastrophization is considered a key clinical symptom in fibromyalgia; however, there are no studies on the pharmacological or psychological treatment of catastrophizing. The general aim of this study is to assess the effectiveness of cognitive-behaviour therapy and recommended pharmacological treatment for fibromyalgia (pregabalin, with duloxetine added where there is a comorbid depression), compared with usual treatment at primary care level.

**Method/design:**

*Design*: A multi-centre, randomized controlled trial involving three groups: the control group, consisting of usual treatment at primary care level, and two intervention groups, one consisting of cognitive-behaviour therapy, and the other consisting of the recommended pharmacological treatment for fibromyalgia.

*Setting*: 29 primary care health centres in the city of Zaragoza, Spain.

*Sample*: 180 patients, aged 18–65 years, able to understand and read Spanish, who fulfil criteria for primary fibromyalgia, with no previous psychological treatment, and no pharmacological treatment or their acceptance to discontinue it two weeks before the onset of the study.

*Intervention*: Psychological treatment is based on the manualized protocol developed by [name] et al, from the University of New Jersey, for the treatment of somatoform disorders, which has been adapted by our group for the treatment of fibromyalgia. It includes 10 weekly sessions of cognitive-behaviour therapy. Pharmacological therapy consists of the recommended pharmacological treatment for fibromyalgia: pregabalin (300–600 mg/day), with duloxetine (60–120 mg/day) added where there is a comorbid depression).

*Measurements*: The following socio-demographic data will be collected: sex, age, marital status, education, occupation and social class. The diagnosis of psychiatric disorders will be made with the Structured Polyvalent Psychiatric Interview. Other instruments to be administered are the Pain Catastrophizing Scale, the Hamilton tests for Anxiety and for Depression, the Fibromyalgia Impact Questionnaire (FIQ), the EuroQuol-5 domains (EQ-5D), and the use of health and social services (CSRI). Assessments will be carried out at baseline, 1, 3, and 6 months.

*Main variable*: Pain catastrophizing.

*Analysis*: The analysis will be per intent to treat. We will use the general linear models of the SPSS version 15 statistical package, to analyse the effect of the treatment on the result variable (pain catastrophizing).

**Discussion:**

It is necessary to assess the effectiveness of pharmacological and psychological treatments for pain catastrophizing in fibromyalgia. This randomized clinical trial will determine whether both treatments are effective for this important prognostic variable in patients with fibromyalgia.

**Trial registration:**

Current Controlled Trials ISRCTN10804772

Fibromyalgia is a prevalent and disabling disorder characterized by a history of widespread pain for at least three months and patient reporting of tenderness in at least 11 of 18 defined tender points when digitally palpated with about 4 kg per unit area of force [21]. Catastrophization is considered a key clinical symptom in fibromyalgia and, in fact, the most used classification of fibromyalgia clinical subtypes includes catastrophization as one of the discriminating variables [22]. However, despite its importance, there is only one study on the psychological treatment of catastrophizing in which the only outcome assessed is the general satisfaction of the patient and his/her knowledge about catastrophizing [23]. Our group has long experience in the treatment of somatoform disorders/fibromyalgia [24,25] and has developed a pioneer psychological treatment of catastrophizing that has proven effective in pilot studies [26].

## Methods/Design

### Objectives

The general aim of the present study is to assess the effectiveness of cognitive-behaviour therapy and recommended pharmacological treatment for fibromyalgia (pregabalin, with duloxetine added where there is comorbid depression), compared with usual treatment at primary care level. The specific objective is to determine the factors (mainly depression and pain) that predict the response of catastrophizing to these treatments.

### Design

This is a multi-centre, controlled trial with a random allocation of patients into three alternative branches (see Figure 1):

**Figure 1 F1:**
[figure not shown]
**Flowchart: randomization, sampling and monitoring of patients**.

1. Cognitive-behaviour treatment

2. Recommended pharmacological treatment (pregabalin), associated to antidepressant (duloxetine) if there is a comorbid depression.

3. Treatment as usual at primary care level.

The evaluation of the treatment outcomes will be performed at patient level and they will be assessed individually.

### Setting and study sample

Patients will be recruited from any of the 29 primary health care centres in the city of Zaragoza, Spain. Patients will be recruited by doctors working in these primary care centres until the required sample is completed, without a quota of patients assigned for each centre.

Patients considered for **inclusion **are those aged 18–65 years, able to understand and read Spanish, who fulfil criteria for primary fibromyalgia according to the American College of Rheumatology [21], no previous psychological treatment, no pharmacological treatment or their acceptance to discontinue it two weeks before the onset of the study, and sign informed consent. Those **excluded **will be patients with severe Axis I psychiatric disorders (dementia, schizophrenia, paranoid disorder, abuse of alcohol and/or drug disorders), severe Axis II disorders from the clinician point of view that prevent from following the treatment protocol, pregnancy or lactation, and refusal to participate.

### Randomization, allocation and masking of study groups

Each patient will be allocated to either one of the three groups using a computer-generated random number sequence. The allocation will be carried out by an independent person, belonging to REDIAPP (Research Network on Preventative Activities and Health Promotion), who is not involved in the study. The method used to implement the random allocation sequence will be a central telephone. The sequence will be concealed until interventions are assigned. Patients agree to participate before the random allocation and without knowing which treatment they will be allocated to. Pharmacological treatment will be administered by one psychiatrist ([name]). Study personnel conducting psychological assessments ([name]) will be masked to participants' treatment conditions.

#### Intervention

##### Psychological intervention

Manualized protocol developed by [name] et al, from the University of New Jersey, for the treatment of somatoform disorders, which has been adapted by our group for the treatment of fibromyalgia [26]. It includes 10 weekly sessions of cognitive-behaviour therapy.

##### Pharmacological intervention

In this group of patients, pregabalin (300–600 mg/day), the recommended treatment for fibromyalgia will be administered, associated with duloxetine (60–120 mg/day) for the patients in whom a major depression disorder is diagnosed [27]. Pharmacological treatment will be administered and followed-up by a psychiatrist ([name]).

##### Treatment as usual at primary care level

This group will continue usual care at primary care level.

#### Main outcome variables

In accordance with the aims of the study, the major outcome is pain catastrophizing in patients with fibromyalgia. This construct will be assessed with the Spanish version [20] of the Pain Catastrophizing Scale [6].

#### Secondary variables

-The following socio-demographic data will be collected: sex, age, marital status (single, married/relationship, separated/divorced, and widowed), education (no studies, primary, lower secondary, upper secondary, university), occupation and social class (I, II, IIIN, IIIM, IV and V of the British Registrar General's Scale) [29].

- The diagnosis of psychiatric disorders will be made with the Structured Polyvalent Psychiatric Interview [30], a psychiatric interview developed by our group and extensively used for the study of somatoform disorders, the group in which fibromyalgia is included in psychiatric classifications.

- Hamilton Anxiety Rating Scale (HARS) [31]. This is a clinician-administered rating scale that consists of 14 items. Each item is rated on a 5-point scale (from 0 = no symptoms to 4 = severe, grossly disabling symptoms. Total scores for the HAS range from 0 to 56. A score of >= 14 has been suggested to indicate clinically significant anxiety. It has a Spanish validated version [32]

- Hamilton Rating Scale for Depression (HAM-D) [33]. This is probably the most used observer-rated depressive symptom rating scale. Although the original scale had 21 items, Hamilton suggested scoring only the initial 17 items because the last 4 items either occurred infrequently or described only aspects of the illness. Items are ranked on a scale of 0–4 (items with quantifiable severity) or 0–2 (items that measure symptoms more difficult to assess reliably). The greatest severity is indicated by 2 or 4. The range for the 17-item scale is 0–50. We have used the Spanish validated version [34].

- Fibromyalgia Impact Questionnaire (FIQ) [35]: The FIQ is a 10-item self-report questionnaire developed to measure the health status of FM patients. The first item focuses on the patient's ability to carry out muscular activities. In the next two items, patients are asked to circle the number of days in the past week they felt good and how often they missed work. Finally, the last seven questions (job ability, pain, fatigue, morning tiredness, stiffness, anxiety and depression) are measured by visual analogue scale (VAS). This instrument has a translated and validated Spanish version [36].

- EuroQoL-5D questionnaire (EQ-5D – Spanish version) [37]: Generic instrument of health-related quality of life. It has two parts: Part 1 records self-reported problems in each of five domains: mobility, self-care, usual activities, pain/discomfort and anxiety/depression. Each domain is divided into three levels of severity corresponding to no problems, some problems, and extreme problems. Part 2 records the subject's self-assessed health on a VAS – a 10-cm vertical line on which the best and worst imaginable health states score 100 and 0, respectively.

- Client Service Receipt Inventory – adapted (CSRI – Spanish version) [38]: Questionnaire for collecting information about use of healthcare and social care services, other economic impacts (such as time off work due to illness) and socio-demographic information. The variant used in this study was designed to collect retrospective data on service utilization during the previous six months.

### Statistical methods

#### Sample size

To calculate the sample size, it is necessary to know the effectiveness of pharmacological and psychological on the main outcome variable, pain catastrophizing. Unfortunately, there are no prior published studies on this subject. Based on our clinical experience, we assume this rate will be by 20% [26]. We aim to detect a difference of 20% or more between any of the groups (control and intervention). Accepting an alpha risk of 0.05 and a beta risk of < 0.20 in a bilateral contrast, we would need 55 patients in each group [28]. Calculating 10% of refusals as found in previous studies [27], we will need a sample size of 60, which implies a total sample of 180 patients with fibromyalgia.

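### The 55 patients per group cannot be reproduced from the inputs in the Sample size section, because no comparator rate (or mean difference and SD) is stated, so the claimed power cannot be verified

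*Protocol article*

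**What the plan says.** All the inputs are in the Sample size section of the protocol article. It says that the effectiveness of the drug and psychological treatments on pain catastrophizing must be known, that nothing has been published, and then: "Based on our clinical experience, we assume this rate will be by 20" per cent. The target follows: "We aim to detect a difference of 20% or more between any of the groups (control and intervention"). The error rates are alpha 0.05 and "a beta risk of < 0.20". The result is that "in a bilateral contrast, we would need 55 patients in each group". An allowance is then made ("Calculating 10% of refusals as found in previous studies"), which brings the figure to 60 per group and 180 in total.

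The section gives no control-group rate, does not say whether the 20% difference is absolute or relative, and gives no responder definition, mean difference or SD.

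Other sections describe the outcome differently. Main outcome variables names pain catastrophizing measured by the Spanish PCS. Background treats catastrophizing as a continuous variable. Analysis strategy labels it categorical but assigns it to general linear models.

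**The concern.** A sample-size statement should let a reader recover the number from its inputs. Here one rate and one difference are given, so the second rate can only be 0% or 40% if the difference is absolute. The two options lead to very different sample sizes, and neither is 55.

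What is at stake is the reading of a null result. A reader will take the stated beta at face value and treat a non-significant comparison as reasonable evidence that no 20-point difference exists. If the true rates are nearer 20% v 40%, the trial would miss such a difference more than a third of the time. The wording as a rate adds to this: if the analysis compares PCS scores, a calculation for proportions says nothing about the score difference the trial can detect.

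**Working it through.** **Inputs (all from the Sample size section).** Alpha 0.05, two-sided: z = 1.960. Power 80%: z = 0.842. Difference 0.20. One rate 0.20. Stated result 55 per group, raised to 60.

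**Formula for two proportions (pooled variance under the null).** With p̄ the mean of p1 and p2:

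n = [1.960·√(2p̄(1−p̄)) + 0.842·√(p1(1−p1) + p2(1−p2))]² / (p2−p1)²

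**Attempt to reproduce 55.**

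- 0% v 20%: p̄ = 0.10. n = (1.960·√0.18 + 0.842·√0.16)² / 0.04 = (0.832 + 0.337)² / 0.04 = 34.1, so **35** (44 with continuity correction).
- 20% v 40%: p̄ = 0.30. n = (1.960·√0.42 + 0.842·√0.40)² / 0.04 = (1.270 + 0.532)² / 0.04 = 81.2, so **82**.

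Other methods for 20% v 40%: unpooled 79, arcsine 81, continuity-corrected 91. Departing from the stated two-sided test gives 64 one-sided, or 74 with continuity correction. Using the 20% variance in both arms gives 63 two-sided and 50 one-sided. A three-group chi-square needs 71 to 102, depending on the third rate. A relative 20% difference (20% v 16% or 20% v 24%) needs 1,447 or 1,683. None gives 55.

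**What does give 55.** 7% v 27%: p̄ = 0.17. n = (1.960·√0.2822 + 0.842·√0.2622)² / 0.04 = (1.041 + 0.431)² / 0.04 = 54.2, so 55. A 25-point difference, 20% v 45%, gives 54. The article states neither pair.

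**Power at 55 per group for a 20-point difference.** Power = Φ{[0.20·√n − 1.960·√(2p̄(1−p̄))] / √(p1(1−p1) + p2(1−p2))}.

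| Rates | Power at 55 |
|---|---|
| 0% v 20% | 95% |
| 5% v 25% | 85% |
| 7% v 27% | 81% |
| 7.5% v 27.5% | 79.7% |
| 10% v 30% | 75% |
| 20% v 40% | 63% |
| 30% v 50% | 57% |
| 40% v 60% | 56% |

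Power reaches 80% only when the lower rate is about 7% or less (or, by symmetry, when the higher rate is about 93% or more). With the continuity correction the limit is tighter: a lower rate of 3% needs 53 and 4% needs 56.

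**20% v 40% at the other relevant sizes.** n = 54: Φ[(1.470 − 1.270)/0.632] = Φ(0.315) = 62%. n = 60: Φ[(1.549 − 1.270)/0.632] = Φ(0.441) = 67%.

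**Allowance.** 55/0.9 = 61.1, so 62 per group; 60 × 0.9 = 54. The difference is two patients per group. For 20% v 40% it moves power only from 63% (55 evaluable) to 62% (54 evaluable).

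**Mean PCS with 54 evaluable per group.** Normal approximation: d = (1.960 + 0.842)·√(2/54) = 0.539; with the t distribution, 0.544. Adjusting for baseline PCS multiplies this by √(1−r²): 0.544 × √0.75 = 0.47 for r = 0.5, and 0.544 × √0.51 = 0.39 for r = 0.7. The correlations are assumptions, since the article gives none.

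**The case against.** The strongest reply concerns how far the shortfall can be claimed. A reader might infer that the trial assumes 20% v 40%, needs 82 per group, and therefore has about 62% power. The article does not support that. It states no 40% and no control rate, and its wording attaches the 20% to the effectiveness of the treatments. With 20% as the active-arm rate against nothing in control, 55 per group would be more than enough, at about 95% power. This stands: 62% is conditional on one reading.

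It does not rescue the figure. The target covers a difference between any of the groups, which can include the two active arms. If one active arm has the assumed 20% rate, a 20-point advantage for the other is exactly 20% v 40%.

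A second reply is that the 20% may refer to a score. If it means a fifth of the comparison mean m, 55 per group would fit an SD of 0.20m/0.534, or about 0.37m. This cannot be ruled out, but the article speaks of a rate and gives neither mean nor SD, so the number is no more reproducible on this reading. A responder definition may sit in the full protocol; even so, the published inputs do not yield the published result.

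Two further inferences should be resisted. The allowance is two patients per group short, and its reference to refusals may be loose wording for withdrawal after allocation; neither is a material defect. The single alpha of 0.05 across several contrasts is a separate question that a statistical analysis plan may settle. Its size depends on whether two or three contrasts are meant (about 9% or 12% familywise error if unadjusted), and the argument here does not rest on it.

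**Conclusion.** The point holds as a failure of reproducibility. The stated 55 per group does not follow from a 20% rate, a 20% difference, two-sided alpha 0.05 and beta below 0.20. The inputs give 35 or 82, and 55 requires rates that are not stated. The claimed beta is met only if the lower of the two rates is about 7% or less. If 20% v 40% is meant, power is about 62% with 54 evaluable per group, 63% with 55 and 67% with all 60.

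These figures assume an absolute difference, equal groups, a two-group comparison of proportions and the pooled normal approximation. For 20% v 40% at 55 per group, an exact calculation gives 64% for the chi-square test and 56% for Fisher's test. The article does not establish that the design is underpowered. It establishes that power cannot be verified, and that the outcome in the calculation does not match the score named as the main outcome. Because the trial's size rests on this number, it should be corrected.

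**What to change.** Keep 180 patients and rewrite the Sample size paragraph for the outcome that will be analysed.

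- **If the outcome is the PCS score:** state that 54 evaluable patients per group give 80% power at two-sided 0.05 for a standardised difference of about 0.54 between two groups. If the analysis adjusts for baseline PCS, give the smaller value with its assumed correlation (0.47 at 0.5, 0.39 at 0.7). Convert it to PCS points with the SD from the group's own pilot or validation work, and say whether that difference is worth detecting.
- **If a responder rate is kept:** define response on the PCS, state both rates and which groups they belong to, say that the difference is absolute, and report the power delivered (about 62% for 20% v 40% with 54 evaluable).

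In either case, carry the 10% allowance through correctly (60 less 10% is 54) and say whether it covers losses after randomisation. Make the outcome type in Analysis strategy agree with the choice.

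The cost is one rewritten paragraph and no extra patients. The stated power or detectable effect may become less favourable. For scale, 80% power for 20% v 40% after a 10% loss would take 82/0.9 = 91.1, so 92 per group or 276 in total; the fix does not ask for this.

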##### Cost-utility analyses

Societal cost perspective will be used for the calculation of costs. Direct costs will be calculated by adding the costs derived from any medication and use of health-related services (general practitioner sessions, specialized medical sessions, emergency room sessions, and hospital in-patient stay). The cost of medications will be calculated by determining the price per milligram during the study, according to the International Vademecum (Red Book) 2008–2010, including value-added tax. Total costs of pharmacological treatment will be calculated by multiplying the price per milligram by the daily dose in milligrams and the number of days such treatment is received. Costs derived from the use of health-related services will be calculated considering the Oblikue unit costs database [39]. Indirect costs will be calculated considering the days of sick leave taken and multiplying them by the minimum daily wage in Spain for 2007–2009. Finally, total costs will be calculated by adding direct and indirect costs.

In Spain, the National Health Service (SNS) is financed by general taxes levied by the state. Medical visits and hospital admissions are fully covered by the SNS. Medications prescribed are fully covered for retired persons, with co-payment for those still in the workforce. Sick leave requires a physician's authorization, and patients unable to work continue to receive most of their salary.

When performing cost-utility analyses, two or more therapeutic options are compared in order to determine which one is the best for maximizing the benefits in light of the available resources [40]. This is achieved by calculating the relationship between the costs of a given intervention (e.g. A) and its consequences, expressed in QALYs, compared with another (e.g. B). This relative value is called incremental cost-utility ratio (ICUR), and it expresses the relationship between the costs and effects of one intervention compared with another.

As the duration of the study is only 12 months, neither costs nor outcomes are subject to discounting [40]. Treatment costs during 12 months follow-up will be modelled by a multivariate gamma regression with a log link. Gamma modelling has been suggested as a suitable choice for analysing cost data, taking into account the skewing of the distribution of the cost data [41,42]. QALYs gained in the first and last six months after the start of the programme will be approximated by measuring the area under the curve using the following equation:

The incremental treatment effect on change in EQ-5D utility score for the first 6 months is d_0–6 _and the incremental treatment effect on change in EQ-5D utility score for the last 6 months is d6-12. These incremental treatment effects will be estimated using multivariate ordinary least squares regressions, adjusting for baseline differences among treatment groups. The covariates included in the models will be: age, sex, years of education, employment and marital status, baseline FIQ and EQ-5D utility scores, and type of medication prescribed. To address uncertainty in the ICUR sampling distribution, non-parametric bootstrapping with five thousand replications will be carried out for each treatment comparison [43].

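### The utility regressions adjust for medication type with no time point; as written this conditions the drug-arm contrasts on the randomised treatment itself

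*Protocol article*

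**What the plan says.** The Cost-utility analyses section of the protocol describes two regressions. For costs: "Treatment costs during 12 months follow-up will be modelled by a multivariate gamma regression with a log link". For utility: "These incremental treatment effects will be estimated using multivariate ordinary least squares regressions, adjusting for baseline differences among treatment groups". The sentence after the utility model lists the covariates: demographic items, then "baseline FIQ and EQ-5D utility scores, and type of medication prescribed". The word baseline stands before the FIQ and EQ-5D scores. The medication item has neither a time point nor a coding.

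Other sections fix what medication means in this trial:

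- Pharmacological intervention: "pregabalin (300–600 mg/day), the recommended treatment for fibromyalgia will be administered", with duloxetine added "for the patients in whom a major depression disorder is diagnosed".
- Psychological intervention: "It includes 10 weekly sessions of cognitive-behaviour therapy". No study drug is named.
- Treatment as usual: care stays with the primary care doctor, and the drugs are not specified.
- Setting and study sample: patients must be drug-free or accept stopping their drugs two weeks before the study.
- Analysis strategy: analysis is by intention to treat.

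**The concern.** Covariates in a randomised comparison should be fixed before allocation. Patients come in off medication, so a drug prescribed during the trial follows randomisation, and in the drug arm it is the allocated treatment. A regression holding both the arm and the drug asks what the arm does beyond the drug. That is not the effect of being randomised to the drug, and it does not sit with intention to treat.

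The incremental utility feeds the incremental cost-utility ratio. If the covariate absorbs it, the drug arm can look ineffective on utility for a purely algebraic reason, or the software may drop a term without notice. If the same list serves the gamma cost model, a second problem follows: drug cost is one of the direct costs being modelled, so that model would condition on a component of its own outcome.

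**Working it through.** The protocol gives no figure for this point, so there is none to reproduce. The only input taken from it is 60 patients per arm (Sample size section). Everything else below is an assumption for illustration.

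**1. By hand: drug arm versus usual care, pregabalin coded yes/no.** Everyone in the drug arm takes pregabalin; a share q of usual care does.

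- Squared correlation of arm and covariate: r² = (1 − q)/(1 + q).
- Variance inflation: 1/(1 − r²) = (1 + q)/(2q).
- At q = 0.10 (6 of 60): r² = 0.9/1.1 = 0.818; inflation = 1.1/0.2 = 5.5; the SE is multiplied by √5.5 = 2.35.

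The same result follows directly. The adjusted coefficient compares 60 drug-arm patients with only 6 usual-care patients on the same drug, and √[(1/60 + 1/6)/(2/60)] = √5.5.

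| q | Inflation | SE multiplied by |
|---|---|---|
| 0 | infinite | not identifiable |
| 0.05 | 10.5 | 3.24 |
| 0.10 | 5.5 | 2.35 |
| 0.20 | 3.0 | 1.73 |
| 0.30 | 2.17 | 1.47 |

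**2. Simulation, three arms.** 60 per arm, 2000 runs. Assumed: utility SD 0.20, CBT effect 0.04, pregabalin effect 0.10, 30% of the drug arm on duloxetine, no drugs in the CBT arm. Medication has four levels: none, pregabalin, pregabalin with duloxetine, other.

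| Usual care | Drug vs usual care, unadjusted (SE) | Adjusted (SE) | CBT vs usual care, unadjusted | Adjusted |
|---|---|---|---|---|
| A: no pregabalin, 60% other drugs | 0.100 (0.037) | not identifiable (rank 5 of 6) | 0.040 | not computed |
| B: 10% pregabalin, 50% other | 0.091 (0.037) | −0.002 (0.093) | 0.029 | 0.039 |
| C: 30% pregabalin (10 points with duloxetine), 40% other | 0.070 (0.037) | 0.000 (0.055) | 0.010 | 0.041 |
| D: all on other drugs | 0.100 (0.037) | not identifiable (rank 4 of 6) | 0.041 | not identifiable |

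In B the model could be fitted in 99.8% of runs, and the SE ratio is 0.093/0.037 = 2.5. It exceeds 2.35 because the four-level coding leaves fewer comparable patients. A separate two-arm simulation (54 per arm, effect 0.08, SD 0.25, 10% of usual care on pregabalin) agrees: 0.072 (SE 0.048) becomes 0.002 (SE 0.121).

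**3. Drug versus CBT, by subtraction in B.** Unadjusted: 0.091 − 0.029 = 0.062, close to the assumed 0.10 − 0.04 = 0.06. Adjusted: −0.002 − 0.039 = −0.041, which is minus the assumed CBT effect. The pregabalin part has gone.

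**4. With the covariate dropped.** The unadjusted columns are that model. It has full rank, and its drug-arm estimates are the assumed effect diluted by pregabalin use in usual care: 0.10 × 0.9 = 0.09 in B and 0.10 × 0.7 = 0.07 in C. That is the intention-to-treat effect.

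**The case against.** The best defence is that pre-study medication was meant. The covariate list follows directly on a clause about "adjusting for baseline differences among treatment groups", and the other items are baseline measures or naturally taken at baseline. Entry admits both untreated patients and patients who stop their drugs, so prior medication does vary before randomisation. This reading cannot be excluded. But the item has no time point, and a reference to prescribed medication sits awkwardly beside entry off drugs. An analyst following the text could well use on-trial drugs. Nor is this a detail left to a fuller document, because the article itself states the covariate list.

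The size also depends on coding. If the item only distinguished pregabalin with duloxetine from pregabalin alone, with 18 of 60 drug-arm patients on duloxetine and none elsewhere, the arm effect would be estimable with an SE ratio of √[(1/42 + 1/60)/(2/60)] = 1.10. That stands, although the contrast would then describe only drug-arm patients without duloxetine. The near-zero adjusted effect is likewise built into the simulations, which route the whole drug effect through the covariate. It shows the mechanism and does not predict this trial's result.

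A reader might infer that every economic contrast is destroyed. The documents do not support that. Medication outside the drug arm is not set by allocation. In B and C the CBT contrast with usual care is shifted, and it is lost only where drug use separates those two arms completely, as in D. A reader might also infer that the cost model certainly uses the list. The wording makes this likely but not explicit.

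**Conclusion.** The point stands for the drug-arm contrasts in the utility regressions. Taken as written, the covariate is post-randomisation and fixed by allocation in that arm. Drug versus usual care and drug versus CBT would then lose the drug-mediated effect, or be non-identifiable when nobody else takes pregabalin and the coding isolates its users.

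The SE inflation for drug versus usual care runs by hand from 1.47-fold (30% of usual care on pregabalin) to 3.24-fold (5%), under an assumed yes/no coding. The protocol states neither the coding nor the crossover, so no single figure can be claimed for this trial. CBT versus usual care changes estimand and may be biased. The effect on the cost model is conditional on the list applying there.

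The reach is limited to the secondary cost-utility analysis. The primary outcome, pain catastrophizing, has its own models in the Analysis strategy section, and this covariate is not among the variables named there.

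**What to change.** Delete the medication-type item from the covariates of the economic models, so that only variables fixed before randomisation remain. If pre-study medication was intended, keep the item but define it explicitly as medication before randomisation, with its categories. State in the same sentence whether the list applies to the utility regressions only or also to the gamma cost model.

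The cost is one line of analysis text. Deleting the item needs no extra data and no patients.
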